## List of Abbreviations:

AE: Adverse Events

BPD: Bronchopulmonary Dysplasia

BW: Birth Weight

CRF- Case Report Form

ELGAN: Extremely Low Gestational Age Neonates

GA: Gestational Age

IVH: Intraventricular Hemorrhage

NEC: Necrotizing Enterocolitis

NICU: Neonatal Intensive Care Unit

NIRS: Near Infra-Red Spectroscopy

PDA: Patent Ductus Arteriosus

PVL: Periventricular Leucomalacia

RAH: Royal Alexandra Hospital

RCT: Randomized Controlled Trial

ROP: Retinopathy of Prematurity

rScO2: Regional Cerebral Oxygen Saturation

SAE: Severe Adverse Events

TNE: Targeted Neonatal Echocardiography

VIS: Vasoactive-Inotropic Score

VVR: Vasoactive-Ventilation-Renal

## Background:

Neonatal transition from the intra-uterine to extra-uterine environment is a complex, multi-organ process. Of the cardiovascular system, the heart of term neonates is anatomically and functionally mature to make the transition. However, the feto-neonatal transition of extremely low gestational age neonates (ELGAN) may have significant challenges in the context of the physiologically “less than adequate” myocardial function and a delicate balance between pulmonary and systemic blood flow. Further, the brain and cerebrovascular state of ELGAN are particularly vulnerable to the effects of an unbalanced transition. Despite advances in neonatal intensive care that have contributed to a decline in mortality and morbidity, preterm birth remains a major cause of mortality and long-term neurological sequelae. Brain injury in preterm infants is often caused by disturbances in cerebral blood flow and oxygenation that happen early in the transition when the majority of intraventricular bleeds and parenchymal infarcts occur. Therefore, it is important to evaluate the systemic and regional hemodynamic state of ELGAN in order to facilitate the neonatal transition.

Neonatal clinicians assess the hemodynamic status of the infant using clinical signs and physiological parameters including heart rate, blood pressure, capillary refill time, urine output and laboratory parameters (base deficit and lactate). While urine output and laboratory parameters do not provide real-time assessment of the hemodynamic status, heart rate and capillary refill time could be non-specific, inaccurate, and observer-dependent, respectively. Blood pressure continues to be used as a common physiological marker for cardiovascular state in neonates. However, there is an increasing amount of evidence that monitoring blood pressure alone is not enough to ensure adequate systemic and cerebral perfusion and oxygenation. Indeed, preterm babies may have “low blood pressure” triggering pharmacological treatment while still maintaining adequate systemic flow, especially cerebral and other organ perfusion as shown by other noninvasive measures like targeted neonatal echocardiography (TNE) and near infrared spectroscopy (NIRS). Interestingly, Baton et al demonstrated that independent of early blood pressure changes, anti-hypotensive therapy exposure in ELGAN was associated with an increased risk of death/neurodevelopmental impairment at 18-22 months corrected age even after controlling for risk factors known to affect survival and neurodevelopment.

The use of TNE by neonatal clinicians to evaluate cardiovascular state in neonates is common in many tertiary neonatal intensive care units. When used in combination with clinical findings, neonatal echocardiography may be an invaluable tool for the identification of hemodynamic compromise, guiding therapeutic intervention, and monitoring treatment response. There are an increasing number of

prospective studies that highlight the potential merits of TNE in identification of cardiovascular compromise and guiding neonatal cardiovascular care . In addition, it has been shown that the use of early echocardiography to provide targeted PDA treatment may result in a reduction of severe intraventricular hemorrhage and pulmonary hemorrhages . The role of TNE to study organ blood flow including cerebral, renal and the gut is largely limited.

NIRS is a technique that can be used to monitor regional cerebral oxygen saturation (rScO2), being both a measure of cerebral oxygenation as well as a surrogate of cerebral blood flow . NIRS monitoring can be applied for prolonged periods of time, even in the most vulnerable infants . It uses multiple wavelengths of NIR light and relies on the distinct absorption spectra of oxygenated and deoxygenated. NIRS offers the ability to assess target organ blood flow. It offers additional information regarding organ perfusion, which supplements data provided by echocardiography and other modalities . In preterm infants, NIRS-derived fractional tissue oxygen extraction and regional cerebral oxygen saturation reference values, particularly over the first 72 hours of life, are emerging . NIRS is being used in many centers including ours, in an ad-hoc manner. In a multicenter, randomized, controlled trial, infants monitored with NIRS and treated for evolving cerebral hypoxia had a lower cerebral hypoxic burden when compared with infants who were not treated based on NIRS findings . The long-term benefit of this approach has yet to be elucidated.

There have been attempts to combine the TNE and NIRS studies in preterm neonates to guide management, showing benefits including reduced inotrope use and length of stay. There is a clear need for a systematic evaluation of the hemodynamic state using a combination of TNE, NIRS and clinical assessment that will result in better clinical understanding of the physiology especially during the transitional period by the neonatal clinicians. The assessment of ELGAN hemodynamics without considering data regarding systemic flow, cardiac output and organ perfusion is incomplete and may result in unnecessary and potentially harmful management strategies.

Various scoring measures have been used in neonates and children to objectively categorize the cardiovascular support using inotrope use as a surrogate. Vasoactive inotrope score (VIS) which provides a numerical sum of inotrope doses used, has been used in preterm infants to quantify cardiovascular support in the perioperative period . A more comprehensive score: Vasoactive Ventilation Renal Score (VVR) that incorporates ventilation support and renal function assessment has been used to evaluate children during the perioperative period . There are no neonatal studies using VVR Scores in the transitional period after birth.

The hypothesis is that having a detailed hemodynamic understanding using a multimodal assessment will result in better cardiorespiratory and renal health at 1 week in ELGAN as evidenced by lower VVR Scores.

## Rationale:

Using mean BP alone as the indication of treatment of neonatal cardiovascular compromise without taking into consideration the status of tissue perfusion may lead to unnecessary exposure of neonates to vasoactive medication. This medication can be potentially harmful to these extremely vulnerable patients. Analysis of a large neonatal database  has demonstrated that treatment of hypotension was associated with an increase in serious brain injury. This held true even after the blood pressure was included in the regression mode, suggesting that it is treatment of hypotension, rather than the presence of hypotension which is harmful. The common interventions, fluid boluses followed by inotropes, could as well be harmful. Observational data has shown an association of fluid boluses with intracranial bleeding and in animal models intraventricular hemorrhage after hypotension can be induced by rapid volume infusion. Fluctuations in blood pressure when inotropes are introduced are well known and could also trigger hemorrhage. Current standard approaches to evaluation and treatment of transitional circulatory problems in the preterm infant may be harmful. Therefore, it is essential that these approaches are adequately investigated.

## Trial Objectives:

### Primary Objective

To determine whether a multimodal hemodynamic monitoring using combined TNE and cerebral NIRS can reduce inotrope use as evidenced by decreasing VVR Scores in ELGAN within the first one week of life.

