### Study Procedure:

This will be a Non-Blind Randomized Control Trial.

The study will involve the following steps ([APPENDIX 1](#)):

- 1) The study population will be assigned by simple randomization to either Multimodal arm to receive multimodal hemodynamic assessment using the study guideline ([APPENDIX 5](#)) or Standard arm to be treated according to the standard approach operative in RAH NICU.

- 2) ELGANs recruited into Standard arm will have
  - a) Continuous cardiorespiratory monitoring using ECG leads or via an Arterial line, and pulse oximetry and intermittent non-invasive blood pressure monitoring as standard of care in the NICU. Continuous arterial blood pressure monitoring will also be obtained as appropriate when an arterial line has been placed under the clinical team's discretion.
  - b) TNE studies will be performed at the discretion of clinical team for concerns on cardiorespiratory status of the study population.
  - c) The current treatment protocol for hemodynamic compromise at our NICU is starting inotropic support if mean blood pressure (MBP) is less than the gestational age of the infant in the first 72 hours of life.
  - d) Cerebral NIRS monitoring for rScO2 using neonatal sensors is not routinely used in the NICU and its application for the standard arm will be up to clinical team discretion.
- 3) ELGANs recruited to the Multimodal arm will have the same monitoring outlined in 2a in a standardized manner.
  - a) Continuous cerebral NIRS monitoring for rScO2 using neonatal sensor will be attached to the forehead of the infant for first 72 hours of life ([APPENDIX 2](#)).
  - b) Hemodynamic assessment using TNE ([APPENDIX 3](#)) will be performed at 18-24 hours and 66-72 hours of life. Additional TNE studies will be performed at the discretion of the clinical team for concerns on cardiorespiratory status of the study population.
  - c) Zubrow's Normative BP chart will be used and MBP less than the third centile for the gestational age will be taken as low BP for the study.
  - d) Blood pressure values and NIRS data will be integrated along with the clinical/biochemical information every 6 hours as well as whenever there is a deviation from the normal range.
  - e) A comprehensive study guideline comprising of the clinical, biochemical and NIRS data will be used by the study team in such cases to derive to the hemodynamic assessment of the study subject.

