## Outcome Measures

### Primary Outcome

The primary outcome would be VVR Score at 7days in both arms.

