### Secondary Outcomes

Prespecified secondary outcomes include duration of mechanical ventilation, length of hospital stays, bronchopulmonary dysplasia (BPD), necrotizing enterocolitis (NEC), retinopathy of prematurity (ROP), intraventricular hemorrhage (IVH), periventricular leukomalacia (PVL), patent ductus arteriosus (PDA), pulmonary hemorrhage and mortality in hospital.

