**VI = (Ventilator RR) x (PIP - PEEP) x PaCO2 / 1,000**

For patients who were extubated to CPAP at the time of blood gas measurement, VI equaled zero.

For those on High Frequency Ventilation, PIP-PEEP will be replaced by Mean Airway Pressure (MAP) and ventilator RR of 60 (which is the maximum ventilator rate on conventional mechanical ventilation) will be used for the purpose of calculating VI score.

For patients on NIMV, a calculated PIP of 5cmH2O less than the ventilator set PIP will be used to account for attenuation of set ventilator pressures reaching the nares.

The baseline serum creatinine will be subtracted from serum creatinine (Cr) measurement by 72 hours of life which will be labelled ΔCr. For patients in whom 72 hour serum creatinine measurements were less than or equal to baseline, we will record ΔCr = 0. Creatinine will be measured in mg/dL. In our center creatinine is measured in mmol/L. This will be converted to mg/dL to calculate the score as follows:

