**VVR = VIS + VI + (ΔCr x 10)**

**Both VIS and VVR scores have been validated in neonatal population.**

## APPENDIX 5: Comprehensive Study Guideline for Hemodynamic Assessment

[figure not shown]

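### The primary objective asks about inotrope use, but day-7 VVR cannot answer that alone, and the early VIS that could is planned without being named as an outcome.

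*Protocol*

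**What the plan says.** The protocol states its aim in three places.

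- **Background (hypothesis):** multimodal assessment "will result in better cardiorespiratory and renal health at 1 week in ELGAN as evidenced by lower VVR Scores".
- **Primary Objective:** whether the monitoring "can reduce inotrope use as evidenced by decreasing VVR Scores in ELGAN within the first one week of life".
- **Primary Outcome:** "The primary outcome would be VVR Score at 7days in both arms".

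Appendix 4 defines the score as "VVR = VIS + VI + (ΔCr x 10"). VIS is a weighted sum of vasoactive doses and is zero if none is running at the blood gas. VI is built from ventilator rate, pressure difference and PaCO2, and is zero for infants extubated to CPAP. The creatinine part has its own window: "The baseline serum creatinine will be subtracted from serum creatinine (Cr) measurement by 72 hours of life".

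Under Study Procedure, NIRS runs for the first 72 hours and scheduled echocardiography falls at 18-24 and 66-72 hours. The standard arm's rule is "starting inotropic support if mean blood pressure (MBP) is less than the gestational age of the infant in the first 72 hours of life".

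The outcome list begins "Prespecified secondary outcomes include duration of mechanical ventilation, length of hospital stays, bronchopulmonary dysplasia (BPD" and goes on to NEC, ROP, IVH, PVL, PDA, pulmonary hemorrhage and in-hospital mortality. None of these ten items is VIS or inotrope exposure. Item 7 of the Study Procedure nevertheless has VIS and VVR calculated in both arms at admission, 24, 48 and 72 hours and 7 days, and Data Collection and Handling records inotrope requirement through the first week.

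**The concern.** The Rationale rests on avoiding unnecessary exposure to vasoactive drugs, and the primary objective repeats that aim. The measure chosen to answer it differs in two ways.

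- **Construct:** inotropes are one of three added parts. A lower total can come from ventilation or creatinine alone.
- **Timing:** the scheduled monitoring and the standard-arm inotrope rule belong to the first 72 hours, while the primary score is taken at day 7. A vasoactive course started and stopped in between adds nothing to the VIS part of that score.

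Two misreadings follow if the objective is reported as worded. A lower day-7 VVR could be presented as fewer inotropes when inotropes did not change. A null day-7 VVR could be presented as no effect on inotropes when early use fell. The quantity that would settle either question is planned but has no standing among the outcomes.

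**Working it through.** **1. The plan's own figure.** Inputs from Sample Size Calculation for VVR Scores: means 30 and 22.5 (difference 7.5), SD 15, alpha 0.05 two-sided, power 0.80.

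- Normal approximation: n per arm = 2 × (1.960 + 0.842)² × (15 / 7.5)² = 2 × 7.85 × 4 = 62.8, so 63.
- With the t distribution: 63.77, so 64 per arm and 128 in total.

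The stated N = 128 reproduces, with power of 80.1% at 64 per arm. There is no arithmetic error. The 7.5 points are set on the total score, with no split by component.

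**2. Full effect with no inotrope change (assumed VI values).** The protocol gives no VI distribution. Suppose infants with a non-zero VI all have the same value and the rest have zero. The difference in share that yields 7.5 points is 7.5 / VI.

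| Assumed VI | Example (rate × pressure difference × PaCO2 / 1,000) | Difference in share needed |
|---|---|---|
| 15 | 30 × 10 × 50 / 1,000 | 7.5 / 15 = 50 points |
| 24 | 40 × 12 × 50 / 1,000 | 7.5 / 24 = 31 points |
| 30 | 60 × 10 × 50 / 1,000 | 7.5 / 30 = 25 points |

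These are large differences. They show that the route exists, not that it is likely. Smaller ventilation differences would supply part of the 7.5 points.

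**3. Early inotrope reduction not seen at day 7 (assumed rates).** Suppose 30% v 15% of infants have a VIS of 10 at 48 hours.

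- Mean VIS at 48 hours: 0.30 × 10 = 3.0 v 0.15 × 10 = 1.5, a difference of 1.5.
- If a fraction f of treated infants in each arm is still on the same support at day 7, the difference left is 1.5 × f: 0 for f = 0, 0.75 for f = 0.5, and 1.5 for f = 1.

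**4. Power if only VIS differs at day 7.** Keep SD 15 and 64 per arm, and let the arms differ only by the stated number of VIS points (assumed).

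| VIS difference at day 7 | Power |
|---|---|
| 1 | 6-7% |
| 2 | 11-12% |
| 3 | 20% |
| 5 | 47% |
| 7.5 | 80-81% |

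To keep the planned power through inotropes alone, the arms would have to differ by 7.5 VIS points still running on day 7.

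**The case against.** The strongest reply is that the protocol is less disjointed than it looks. The objective itself names VVR as its evidence, and a composite of vasoactive, ventilatory and renal support at one week fits the hypothesis in the Background well. This stands, and it is why the remedy is to reword the objective and leave the primary outcome alone. It does not rescue the words about inotrope use.

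Four stronger readings are tempting, and the document does not support them.

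- **That early inotrope use goes unmeasured.** It does not: VIS is to be calculated in both arms at 24, 48 and 72 hours, and inotrope requirement is recorded all week. An early reduction would be visible in those data. The gap is that they are not designated as outcomes.
- **That VI dominates day-7 VVR.** No VI, VIS or ventilation rates are given. With VI at 24 in every infant, the other parts must still supply 30 - 24 = 6 points of the planned control mean; with VI at 30 in every infant, they need supply none. The balance is unknown.
- **That the score is purely a day-7 snapshot outside the intervention window.** On the only definition given, the creatinine part reflects the first 72 hours. Additional echocardiography and round-the-clock consultation also carry no stated 72-hour limit.
- **That the arms' different blood pressure definitions alone would change inotrope use.** For the multimodal arm, "MBP less than the third centile for the gestational age will be taken as low BP for the study". That defines low pressure and is not stated as an inotrope trigger. What follows from it lies in the figures of Appendices 5 and 8, which are not shown here, so the effect cannot be judged.

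Separate reporting of components could also be left to a statistical analysis plan, which is not at hand. The wording of the objective and the list of prespecified outcomes are fixed in the protocol itself.

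**Conclusion.** The point holds as a mismatch between hypothesis, primary objective and primary outcome, together with an omission from the outcome list. It follows from the definition of the score alone: a day-7 VVR difference does not by itself demonstrate less inotrope use, and a null result does not rule out less use earlier. The sample size is correct for the outcome it addresses.

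The size cannot be fixed from the protocol. The 25 to 50 percentage-point range rests on an assumed VI of 30 down to 15. The power of about 11-20% for a VIS difference of 2 to 3 points rests on that assumed difference, with the planned SD and group size. The 48-hour example rests on assumed treatment rates and on the fraction still treated at day 7. This is worth correcting because it is cheap and protects the interpretation; it does not invalidate the primary analysis.

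**What to change.** 1. Restate the primary objective as the effect of the multimodal strategy on day-7 VVR, described as cardiorespiratory and renal support, so that it agrees with the Background hypothesis and the Primary Outcome.
2. Add to Secondary Outcomes VIS at 24, 48 and 72 hours and any vasoactive exposure to 72 hours. The exposure item matters because three spot scores can miss a course given between them.
3. Rest any statement about inotrope use on that outcome and not on day-7 VVR.
4. Report VIS, VI and ΔCr × 10 separately by arm at day 7, alongside the total.

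The cost is wording in the objectives and outcomes sections. VIS is already calculated at these times and inotrope requirement already recorded, so no new data are needed. The downside is one more secondary comparison and a narrower primary claim.

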### Secondary Objective

To validate the use of VVR Scores during the neonatal transition period in ELGAN population.

## Methods:

### Study Design

Non-Blinded Randomized Control Trial

### Study site

This study will be conducted at the Royal Alexandra Hospital Neonatal Intensive Care Unit (RAH NICU) which is a 69-bed unit that specializes in the care of very premature infants. On average, about 150 ELGAN less than 29 weeks are admitted per year to the RAH NICU for specialized neonatal care.

### Inclusion Criteria

1. Preterm babies less than 29 weeks ELGAN.
2. Babies born in RAH and admitted to RAH NICU for first 7 days of life.

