### Exclusion Criteria:

1. Structural heart diseases.
2. Major congenital disorder or chromosomal disorder.

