## Statistical Plan and Data Analysis:

### Sample Size Calculation for VVR Scores

Assuming 25% reduction in VVR in intervention arm with mean VVR Score of 30 in control arm and 22.5 in intervention arm, sd-15; t test assuming  $sd_1 = sd_2 = sd$ ;  $H_0: m_2 = m_1$  versus  $H_a: m_2 \neq m_1$

Study Parameters:

$\alpha = 0.0500$ ;  $\text{power} = 0.8000$ ;  $\text{delta} = -7.5000$ ;  $m_1 = 30.0000$ ;  $m_2 = 22.5000$

$sd = 15.0000$

Estimated sample sizes:  $N = 128$ ;  $N \text{ per group} = 64$

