### Analysis

All statistical analyses will be performed with the intercooled Stata Version 18.0 (College Station, Texas). All data will be anonymized for analysis and intention to treat analyses will be performed for primary outcome. All the tests will be two-sided (where applicable), and significance will be defined as p-value  $< 0.05$ . Univariate and bivariate analysis will be done to describe the sample. Categorical variables will be compared by Fisher's Exact Test and continuous variables by Student's t-test (two-sided). Logistic and linear regression models will be developed using forward and backward stepwise methods to examine the association between different VVR cut off (95th centile for the entire study cohort and literature derived cut off of  $VVR > 53^{25}$  that is associated with adverse outcomes in neonatal postoperative cardiac patients) and neonatal outcome. ROC curve will be used for the purpose of validation of the VVR Scores in neonates during the neonatal period.

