**serum creatinine (mmol/dL) x 0.0113 = serum creatinine (mg/dL).**

Using each of these individual measurements, the VVR Score at the time of each arterial blood gas measurement will be calculated as follows:

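### Inclusion item 2 can be confirmed only on day 7, after randomisation, which conflicts with intention to treat; with no VVR for infants who die, the day-7 t-test by default compares survivors

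*Protocol*

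**What the plan says.** Inclusion Criteria, item 2, requires: "Babies born in RAH and admitted to RAH NICU for first 7 days of life". Exclusion Criteria, item 1, is "Structural heart diseases", with no statement of when or how this is established.

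Under Study Procedure, the multimodal arm has cerebral NIRS for the first 72 hours and echocardiography (TNE) at 18-24 and 66-72 hours. For the standard arm, item 2b says "TNE studies will be performed at the discretion of clinical team for concerns on cardiorespiratory status of the study population".

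The primary outcome is VVR at 7 days. In-hospital mortality is a separate secondary outcome. The Analysis section states that "intention to treat analyses will be performed for primary outcome" and names Student's t-test for continuous variables.

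Appendix 4 gives zero rules for infants without vasoactive support and for those extubated to CPAP, both at the time of a blood gas. It then says "the VVR Score at the time of each arterial blood gas measurement will be calculated as follows". It assigns no score to an infant who has died. The Consent section allows written consent up to 7 days after delivery.

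**The concern.** Eligibility should rest on facts known at randomisation. A condition that becomes true or false on day 7 can be affected by the allocated strategy. An infant who dies or is transferred on day 3 has been randomised and managed under an arm, yet fails item 2 as worded. Removing that infant contradicts intention to treat.

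The second part is that the outcome is undefined after death. A day-7 score, a t-test on scores and no value for death together leave a comparison of survivors. If VVR tracks severity, as the protocol's plan to validate it against morbidity and mortality presumes, losing more high-scoring infants from one arm makes that arm look better. An arm that saves infants is penalised.

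Unequal echocardiography matters for the same reason. If a heart defect found after allocation could still count as an exclusion, it would be looked for routinely in one arm and only on clinical concern in the other, in an unblinded trial.

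**Working it through.** **Order of events, from the protocol.** Allocation, then NIRS from 0 to 72 hours, TNE at 18-24 and 66-72 hours, then VVR on day 7. Item 2 is verifiable only at the last of these.

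**The plan's own sample size.** Inputs: "mean VVR Score of 30 in control arm and 22.5 in intervention arm, sd-15", alpha 0.05 two-sided, power 0.80.
- Normal approximation: n per arm = 2 × (1.96 + 0.842)² × 15² / 7.5² = 62.8, so 63.
- Noncentral t: 63.77, so 64 per arm and 128 in total. The stated figure is reproduced, with power 0.801.
- This assumes 64 scored infants per arm. If 10% have no day-7 score (64 × 0.90 = 57.6 per arm), power is 0.76. If 20% have none (51.2 per arm), it is 0.71. These rates are assumptions.

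**Bias from losing deaths.** The protocol gives no mortality figure, so what follows is illustrative. Assume VVR is normal with mean 30 and SD 15 in both arms (no effect), and that the infants with the highest scores die. With a fraction d removed from the top, the survivor mean is 30 − 15 × φ(c)/(1 − d), where c = Φ⁻¹(1 − d).
- d = 5%: c = 1.645, φ(c)/(1 − d) = 0.1086, mean 28.37, SD 13.50.
- d = 10%: mean 27.08.
- d = 15%: c = 1.036, φ(c)/(1 − d) = 0.2743, mean 25.89, SD 12.00.

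Deaths of 5% control v 15% multimodal:
- Difference = 28.37 − 25.89 ≈ 2.5 points; 2.5/7.5 is about a third of the planned effect.
- Standard error = √(13.50²/60.8 + 12.00²/54.4) = 2.38, so the shift is 1.05 standard errors and the two-sided rejection rate is about 0.18.
- Simulation with a set number of deaths per arm gives 19-23%. The upper end is partly produced by cutting a set number of top scores from each sample, which itself makes the t-test too liberal.

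Variants:
- 5% v 10%: 28.37 − 27.08 = 1.3 points.
- Death correlated 0.5 with VVR, 5% v 15%: 0.5 × 2.5 ≈ 1.2 points, rejection about 7%.
- Death unrelated to VVR: no bias, rejection 5%.
- Equal deaths of the same kind: no difference between arms.
- Reverse direction, 15% control v 5% multimodal, true benefit 7.5: the survivor difference shrinks to about 5.0 and t-test power to 0.52.

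**Cost of a worst-rank test as primary.** At 10% deaths per arm and a true 7.5-point effect:
- Sickest die: survivor t-test 0.85-0.89 v worst-rank Wilcoxon 0.74-0.75. A variant with random death counts gives 0.81 v 0.73.
- Death unrelated to VVR: 0.76 v 0.60.

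The loss is about 10 to 16 points in most variants.

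**The case against.** The protocol nowhere says that a randomised infant will be removed, and it promises intention to treat. Item 2 may have meant an expected stay. Handling of deaths and missing scores is commonly left to a statistical analysis plan, which is not at hand. Mortality is a prespecified secondary outcome, so an imbalance would be visible. These points stand as limits on the claim. They do not rescue the wording of item 2, which is eligibility text that belongs in the protocol and does not mention expectation.

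Three stronger readings are tempting and are not supported.
- A reader might infer that infants with heart disease found on the scheduled scan will be excluded. The protocol shows unequal opportunity for detection, not exclusion after allocation; diagnosis before randomisation is not ruled out.
- A reader might infer that recovering infants lose their score for want of an arterial sample. Only the final VVR sentence of Appendix 4 says arterial. The zero rules refer to a blood gas of any kind and set VI to zero on CPAP and VIS to zero without vasoactives, and creatinine is taken by 72 hours. The terms are inconsistent; lost scores are not shown.
- A reader might infer that death must be ranked worst in the primary test. That replaces the planned mean difference with a composite of death and score and costs power that the sample size does not cover. The assumption that the sickest die also favours that test by construction.

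**Conclusion.** The point holds in a limited form. As worded, item 2 is a post-randomisation condition that conflicts with the intention-to-treat statement. As defined, the primary outcome has no value for infants who die before day 7, so a survivor comparison is the default consequence rather than a declared plan.

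No estimate of bias follows from the document. The 2.5 points and roughly 20% false positives need both a threefold difference in mortality and death governed by VVR. Weaker and equally admissible assumptions give 1.2 points and 7%, or nothing. Equal loss of similar infants costs power only. The case for changing the wording rests on the contradiction itself and on how little the change costs, not on a predicted size of error.

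**What to change.** 1. Reword inclusion item 2 to *born at RAH and admitted to RAH NICU*, with no 7-day condition.
2. State that the heart-disease and congenital or chromosomal exclusions are judged only on information known before randomisation, and that infants diagnosed later stay in the analysis.
3. Define the primary analysis set as all randomised infants, subject to deferred consent, which is itself a step after allocation; report by arm how many are lost through it.
4. Report deaths before day 7 by arm beside the survivor VVR comparison. Prespecify a sensitivity analysis by Wilcoxon test in which death ranks worse than any observed VVR.
5. Reconcile the arterial and unspecified blood-gas wording in Appendix 4, so that infants on CPAP without vasoactives are scored without an arterial sample.

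The cost is wording and a little extra analysis. The worst-rank test stays a sensitivity analysis because, as primary, it would give up about 10 to 16 power points at 10% deaths per arm.
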